## Abstract

**Background:**

In Australia, secondary school educators are well positioned to recognize mental illness among students and provide support. However, many report that they lack the knowledge and confidence to do so, and few mental health training programs available for educators are evidence based. To address this gap, the Black Dog Institute (BDI) developed a web-based training program (Building Educators’ Skills in Adolescent Mental Health [BEAM]) that aims to improve mental health knowledge, confidence, and helping behaviors among secondary school educators in leadership positions. A pilot study of the training program found it to be positively associated with increased confidence and helping behaviors among educators and reduced personal psychological distress. An adequately powered randomized controlled trial (RCT) is needed.

**Objective:**

The primary objective of this cluster RCT is to evaluate the effectiveness of the BEAM program for improving educators’ confidence in managing student mental health. The trial will also evaluate the effect of the BEAM program in increasing educators’ frequency of providing help to students and improving their mental health knowledge and reducing educators’ psychological distress and stigma toward students with mental health issues.

**Methods:**

The target sample size is 234 educators from 47 secondary schools across New South Wales, Australia. Four waves of recruitment and enrollment into the trial are planned. Schools will participate in one wave only and will be randomized to the intervention or waitlist control conditions. Participants from the same school will be assigned to the same condition. Assessments will be conducted at baseline, posttest (10 weeks after baseline), and follow-up (22 weeks after baseline) using the BDI eHealth research platform. Intervention participants will receive access to the BEAM program for 10 weeks upon completion of baseline, and the control condition will receive access for 10 weeks upon completion of the follow-up assessment.

**Results:**

Recruitment for this trial began on July 21, 2020, with the first baseline assessments occurring on August 17, 2020. To date, 295 participants from 71 schools have completed baseline. Due to the unexpected success of recruitment in the first 3 waves, the final fourth wave has been abandoned. Intervention participants are currently receiving the program, with follow-up due for completion in March 2021.

**Conclusions:**

This is one of the first RCTs to examine the effectiveness of a web-based adolescent mental health training program for Australian secondary school educators in leadership positions. If found to be effective, this training program will offer a sustainable and scalable delivery method for upskilling educators in caring for students’ mental health.

**Trial Registration:**

Australian New Zealand Clinical Trials Registry ACTRN12620000876998; https://covid-19.cochrane.org/studies/crs-14669208

**International Registered Report Identifier (IRRID):**

DERR1-10.2196/25870

## Introduction

### Background

Over half of all mental illnesses experienced by adults begin before the age of 18 years [1], yet many young people have difficulty recognizing the early signs and symptoms [2,3]. Unfortunately, many of these young people do not actively seek professional help (eg, from school counselors or psychologists) [4-6]. As secondary schooling is compulsory in Australia, educators are well positioned to identify changes in students’ mental health, offer support, and facilitate access to treatment services [7-9]. However, many report that they lack the confidence and knowledge to recognize and respond to mental health issues among their students [7,10,11]. Educators also report that the increased responsibilities and expectations of caring for students’ mental health increases their levels of work-related stress and psychological distress [12,13]. Thus, there is a clear need for mental health training to improve mental health outcomes for students and to reduce personal stress for educators.

Despite the recommendation by government bodies for greater training in adolescent mental health [14,15], there are very few evidence-based training programs available to educators about student mental health. Recent systematic reviews have identified 6 training programs, only 1 of which was assessed in the Australian context (adult and youth versions of Mental Health First Aid [MHFA]) [16,17]. Of the remaining 5 programs, the Mental Health High School Curriculum Guide teacher training program [18,19], the Go-to Educator Training [20], and The Guide Pre-Service Professional Development Program [21] were all assessed in Canada; the Teachers As Accompagnateurs (TAPS) [22] in Haiti; and the African Guide: Malawi Version [23] in Malawi. All programs provided teachers with information about the common adolescent mental health issues, along with associated signs and symptoms, and directed teachers to additional resources and services. Only the MHFA and TAPS programs provided additional information for teachers on how to identify and support students experiencing a mental health crisis. Of the 6 identified programs, only 1 was assessed using a randomized controlled trial (RCT) methodology, with the remaining 5 employing noncontrolled pre-post designs.

Although all 6 programs were shown to be effective for improving mental health knowledge, none have yet been shown to be effective in increasing helping behaviors, for example, recommending or referring a student to seek professional help, or in reducing the distress experienced by educators [24,25]. In addition, these programs are typically delivered through face-to-face, didactic-style workshops, requiring educators to take leave to attend [24,25]. This may be a barrier to large-scale uptake and increase the financial burden for schools, as they are required to find replacement teachers. With the advancement of technology and effective digitally delivered mental health training programs being developed for workplace settings (eg, refer to the study by Gayed et al [26]), there is an opportunity to develop mental health training for educators that is delivered in new ways.

To fill this gap, the Black Dog Institute (BDI) developed the Building Educators’ Skills in Adolescent Mental Health (BEAM) program. BEAM is a web-based training program on adolescent mental health for secondary school educators in leadership positions, such as year advisors, heads of well-being, and principals*.* To accurately identify educators’ training needs, the BEAM program was initially developed in collaboration with an advisory group of teachers in general teaching and leadership roles. The group consisted of 12 school teachers from various secondary schools located in New South Wales (NSW), Australia. BEAM was originally designed for year advisors, given their role in maintaining student engagement and the well-being of an entire cohort of students. They also often act as case managers, linking students with services and resources when needed, and are usually the first point of contact for parents and teachers. However, there is no formal training for this role, and it is performed in addition to their regular teaching duties. Research on workplace mental health has indicated that training programs for managers can improve their mental health knowledge, thereby improving their confidence and increasing their helping behaviors toward their staff’s mental health needs [26-28]. Furthermore, as nonstigmatizing attitudes have been shown to be associated with intentional or actual contact with individuals with known mental illnesses [28,29], improving stigma may also help increase the assistance provided to students. Therefore, the BEAM program aims to model this workplace mental health research [26-28] while also reducing educators’ stigmatizing attitudes toward students with mental illness. BEAM consists of 5 self-paced and self-directed modules on adolescent mental health (Multimedia Appendix 1), including quizzes, blog style story sharing, and case studies. The program also includes informal, nonmandatory, peer coaching activities that encourage participants to meet with a colleague to discuss the program and apply the content to their own school context. By blending web-based content with face-to-face peer learning, the program aims to foster professional relationships, consolidate learning, and facilitate new problem-solving skills [30]. This flexible model allows users to complete the program at a time that is convenient for both the educator and their school without the educator having to take leave to attend face-to-face workshops.

A recent pilot study examined the acceptability of the BEAM program among secondary school year advisors (N=71) from NSW, Australia. After using the program for 6 weeks, the year advisors reported significantly higher levels of self-reported confidence in their ability to care for students’ mental health and lower levels of personal psychological distress. Year advisors also reported an increased frequency of helping behaviors at the 19-week follow-up. However, many of the year advisors did not complete the entire program (59/70, 84%) reporting that the 6-week duration was insufficient, and barriers such as forgetfulness hampered their completion. In preparation for this trial, several modifications were made to the program to increase engagement and completion: program access was extended to 10 weeks, SMS reminders in addition to email reminders were embedded, sequential module completion was removed so that participants can complete the modules in any order, a *module suggestion* function was embedded that encourages the participant to complete modules based on their interest, and the program was optimized for completion on both mobile and desktop devices to increase accessibility. The eligibility criteria for BEAM have also been extended to encompass other leadership roles within the school, including principals, heads of well-being, and directors of pastoral care, among others. This decision was made because these staff members also have responsibilities regarding student well-being in addition to their regular teaching duties and are well placed to influence schools’ policies and possibly enact change. The program is now ready to be evaluated for its effectiveness using an RCT.

### Objectives

The primary objective of this trial is to evaluate the effectiveness of the BEAM program in improving secondary school educators’ confidence in recognizing and responding to their students’ mental health needs. The secondary objective is to assess BEAM’s effectiveness in increasing the frequency of help provided to students, improving educators’ mental health knowledge, reducing educators’ stigma toward others with mental illnesses, and reducing their own psychological distress.

### Hypotheses

The primary hypothesis is that educators who are allocated to receive the BEAM program will report significantly higher levels of confidence at posttest (primary endpoint) when compared with the waitlist control condition and that these effects will be sustained at follow-up. It is also hypothesized that educators who receive the BEAM program will report greater improvements in mental health knowledge, stigma, and psychological distress at posttest and a greater frequency of helping behaviors at follow-up, when compared with those in the control condition.

## Methods

### Design

This study is a cluster randomized controlled effectiveness trial with 2 parallel conditions (the BEAM program and waitlist control), with measurements taken at baseline, posttest (10 weeks from baseline completion), and follow-up (22 weeks from baseline completion). This study protocol was approved by the primary ethics body of the University of New South Wales (UNSW) Human Research Ethics Committee (HREC; HC200257). Approval was also sought and obtained from the NSW Department of Education State Education Research Applications Process (SERAP2020222) to conduct research within government schools and from the Catholic Schools Office Dioceses of Maitland-Newcastle, Canberra-Goulburn (schools located in the Goulburn area only), and Wollongong to conduct research with schools located within their dioceses.

This research project is also guided by a trial management committee consisting of experts in research and trial design and service and program implementation to oversee and provide guidance on the study procedures. This committee meets bimonthly or more frequently on an as-needed basis.

### Participants

#### Inclusion Criteria

To be eligible to participate, secondary school educators must be (1) employed in a school leadership position that includes responsibility for student well-being (eg, year advisors, directors or heads of student well-being, principals, directors of pastoral care, student coordinators, and heads of year); (2) currently working in this role at a government, Catholic, or independent secondary school in NSW, Australia, for the duration of the study; and (3) obtain their principal’s consent for their involvement.

#### Exclusion Criteria

Secondary school educators who participated in the pilot study are not eligible to participate in this trial.

### Sample Size

The target sample size for this trial is 234 participants from at least 47 schools. This calculation is conservatively based on the participation of an average of 5 educators per school and an intraclass correlation of 0.07, which yields a design effect of 1.28. To detect a standardized effect size of 0.50, (a minimum of a moderate effect size is required to warrant future value and benefit of the program) with 80% power and α=.05 (2-tailed), an individually randomized trial would require 64 participants per arm. This number is inflated by the design effect to 82 to allow for clustering, with the recruitment increased to conservatively allow for attrition of up to 30%. This yields a minimum of 117 participants per arm.

### Randomization and Blinding

Cluster randomization at the school level is used to avoid potential contamination and bias effects from other participants, reduce administrative tasks for schools, and enable implementation of the peer-to-peer component of the program. As such, all participants from the same school will be allocated to the same condition and complete the trial at the same time using randomly permuted block randomization with block sizes of 2 and 4. Schools will be assigned to either the intervention or control arm using a 1:1 allocation, stratified by school size (<400 or >400 students) and index of community socioeducational advantage (ICSEA) level (<1000 or >1000) as per a computer-generated randomization schedule. Randomization is conducted by a statistician not involved in the day-to-day running of the trial to avoid influence or bias. The research team will be aware of the allocation once registration is scheduled to begin because they are responsible for providing the link to participants for the intervention or control program study website. Participants will be unaware of which group they are allocated to during registration and baseline. Upon completion of baseline, they will be informed, via email, of their allocation. This is because the intervention participants will receive immediate instructions and access to the program, and the waitlist control participants will be asked to wait for their next survey.

### Recruitment

Multimedia Appendix 2 outlines the recruitment, randomization, and procedure for this trial.

A passive approach to recruitment is being undertaken using study advertisements. The advertisements are being placed on the BDI’s website and social media channels (Facebook, LinkedIn, and Twitter), within BDI newsletters, and circulated to BDI mailing lists and contacts. The study is also being advertised in the NSW Health School-Link e-newsletters (an NSW Health service that connects schools with local mental health services), Teacher Magazine, and Catholic Diocese bulletins. After viewing the study advertisements, interested educators are directed to a web-based expression of interest form on the BDI website, which collects their name, school, suburb, email, and role at their school. Once registered, prospective participants are encouraged to share the study information with their colleagues to increase cluster sizes and encourage peer-to-peer interaction. To promote a representative sample from metropolitan, regional, and rural locations, participation will be open to all government, Catholic, and independent schools within the Australian state of NSW for which we have ethical approval.

### Consent

#### Principal Consent

After expressing interest, the educators are emailed the study information. Interested participants consult their principal to obtain a signed letter of support. The school and its educators are randomized after the letter of support is received by the research team. Only 1 signed letter of support is required per school.

#### Educator Consent

Educator consent is obtained online. Prospective participants provide consent by confirming the declaration statements in the web-based participant information sheet and consent form (PISCF). Participants can download the PISCF before providing consent, and they are emailed a copy for their records.

#### Withdrawal of Consent

Participants can withdraw consent at any time without providing a reason by contacting the research team, replying to any email communication with the word *withdraw*, or completing the withdrawal form located within the PISCF. When a participant withdraws, all study data are retained, but no further data are collected, and all study communication ceases.

### Procedure

#### Registration

This trial will include 4 waves of registration and enrollment. A predetermined cut-off date indicates which wave a school participates in, as determined by the date on which the letter of support is received. Using waves ensures that data collection does not occur during summer school holidays, allows flexibility for when schools enroll in the trial based on their schedule, and ensures that participants from the same school commence the trial concurrently. Once all registered participants from a single school commence the baseline survey, no other prospective colleagues from that school can register. This prevents the influence that knowledge of group allocation might have on future participant enrollment. To avoid disappointment, educators are asked to tell their colleagues about the study at the time of recruitment.

Participants are sent an email directing them to the study registration website 1 week before the scheduled baseline start date. Here, they are asked to confirm their eligibility, register their personal details (including their name, school, and email), provide consent, and create a study account. They have the option to enter their mobile phone number to receive SMS notifications and reminders. Once completed, they await further instructions and access to the baseline survey.

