#### Baseline, Posttest, and Follow-Up Assessments

On the day each wave is due to begin, participants receive an email (and optional SMS) inviting them to complete the baseline survey. The survey is accessible for 7 days, and participants who do not complete it are automatically withdrawn. This process is repeated for the 10-week and 22-week assessments. All participants receive 2 email reminders (and 2 optional SMS reminders) for the survey completions.

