Despite these limitations, this trial has several strengths, including the RCT design to examine the effectiveness of BEAM and the clustering and randomization at the school level to reduce the risk of bias and contamination. Once a school begins in the trial, no other educators from that school can enroll, ensuring that participants are not influenced by the participation of other staff members from their school. The standardized delivery of the intervention helps maximize the fidelity of the training being delivered to educators, ensuring that all participants receive the same standardized intervention. Other strengths include the suite of measures included to examine a range of outcomes; the long-term follow-up period; targeted recruiting approach to include educators from metropolitan, regional, and rural areas; exploration of possible moderators; and stratification of school variables to account for factors hypothesized to influence the results. If shown to be effective, the assessment of BEAM through an RCT will provide a novel method for delivering mental health training to secondary school educators.

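### As worded, the registration lock can close a school after its arm is already known there, so it does not guarantee the protection claimed for it

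*Protocol article*

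**What the plan says.** All of the following is in the protocol article.

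- **Principal Consent:** "The school and its educators are randomized after the letter of support is received by the research team". Registration and online consent follow, so individual enrolment takes place after the school has been allocated.
- **Registration, opening:** "Participants are sent an email directing them to the study registration website 1 week before the scheduled baseline start date".
- **Registration, closing:** "Once all registered participants from a single school commence the baseline survey, no other prospective colleagues from that school can register". The stated purpose is: "This prevents the influence that knowledge of group allocation might have on future participant enrollment".
- **Randomization and Blinding, disclosure:** "Upon completion of baseline, they will be informed, via email, of their allocation". In addition, "all participants from the same school will be allocated to the same condition".
- **Baseline, Posttest, and Follow-Up Assessments:** "The survey is accessible for 7 days, and participants who do not complete it are automatically withdrawn".
- **Limitations and Strengths:** the lock is presented as a strength in other words: "Once a school begins in the trial, no other educators from that school can enroll".
- **Results:** 308 educators registered and 295 completed baseline, from 71 schools. Baseline for waves 1 to 3 is finished and the fourth wave will not run.

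**The concern.** Schools are allocated before their educators register, so the closing rule is the article's stated safeguard against people joining, or not joining, because they know the arm. The rule is keyed to the last registered educator starting baseline. Disclosure is keyed to the first educator finishing it. Nothing in the text puts the first of these events before the second.

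The two arms differ in their appeal to a late joiner. One offers the program at once and the other offers it after 22 weeks. A colleague could register because someone at the school has just received access, or decide not to because the school is on the waitlist. The arms could then differ in the number and motivation of their educators, in a trial whose primary outcome is self-rated confidence. The claim of prevention is made twice, once in the Methods and once as a strength, and a reader would rely on it when judging selection bias.

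**Working it through.** **1. Order of events.** Let S be the time a registered educator starts baseline and L the lag from starting to receiving the allocation email.

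- First disclosure in the school = min(S) + L, taking the same L for everyone.
- Closure under the Registration section = max(S).
- Registration is open with the arm known whenever max(S) > min(S) + L.

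With one educator, max(S) = min(S) and the gap never opens. With two or more, the gap opens whenever their starts are further apart than L. Because the survey is open for 7 days, the gap is limited to just under 7 days. The predetermined cut-off date in the Registration section does not shorten it, because that date concerns receipt of the letter of support and fixes the school's wave. No other closing point for educators is given.

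**2. Registrants who never start.** Read literally, one such registrant leaves the trigger unmet until automatic withdrawal at day 7. In the Results, 308 − 295 = 13 registrants (13/308 = 4.2%) did not complete baseline. The article does not say how many of them never started.

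**3. How often the gap could open.** No figure in the plan is in dispute. The sample-size section assumes 5 educators per school, and its arithmetic reproduces: 1 + (5 − 1) × 0.07 = 1.28; 64 × 1.28 = 81.92, rounded to 82; 82/0.70 = 117.1, stated as 117. The achieved mean is 295/71 = 4.15 completers per school, but the spread of school sizes is not given.

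A simulation used independent start times, either uniform over 7 days or front-loaded (exponential with mean 1 day, capped at 7). The start times and the lag are both assumptions, not figures from the article. The table shows the share of schools in which the last start falls after the first disclosure.

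| Educators | Lag | Uniform starts | Front-loaded starts |
|---|---|---|---|
| 1 | any | 0% | 0% |
| 2 | 30 min | 99.4% | 98.0% |
| 2 | 2 h | 97.6% | 92.1% |
| 2 | 24 h | 73.4% | 36.9% |
| 5 | 30 min | about 100% | about 100% |
| 5 | 2 h | about 100% | about 100% |
| 5 | 24 h | 99.8% | 84.2% |

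With 5 educators and a lag of 30 minutes to 2 hours, the median open period is 4.7 to 4.8 days (uniform) or about 1.8 days (front-loaded). If colleagues tend to start together, all these figures fall.

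**4. What it could do to the estimate.** Bias ≈ share of late joiners in the BEAM arm × their excess gain. Suppose 5% to 10% are late joiners, with no counterpart in the control arm, and their gain is 0.3 SD larger. Both inputs are assumptions.

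- 0.05 × 0.3 = 0.015 SD, and 0.015/0.50 = 3% of the target effect.
- 0.10 × 0.3 = 0.03 SD, and 0.03/0.50 = 6%.

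A design with 80% power for 0.50 SD at two-sided 0.05 implies a standard error of about 0.50/2.80 = 0.18 SD. The illustrated bias is therefore about 8% to 17% of one standard error.

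**5. The two wordings of the trigger.** The Registration section requires all registered educators to have started. The Discussion refers to the school beginning in the trial and does not define that moment. If it means the wave's start date or the first educator's start, closure comes before any disclosure and the claimed protection holds against disclosure by a colleague. If it means that everyone has started, the gap in step 1 remains.

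**The case against.** The strongest reply is that the authors probably meant closure when the wave starts. The Registration section says that educators from one school commence concurrently, and the baseline invitation goes out on a single day. On that reading the Methods and the Discussion describe the same moment. A reader might infer a flat contradiction between them. The documents do not support that, because the Discussion's term is undefined. What stands is that the Methods sentence names a later event than a wave start, and the 7-day window with reminders allows staggered starts.

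A reader might also infer that the lock always comes too late. It does not. Single-educator schools are unaffected, and so are schools where everyone starts before anyone has finished and been told. The high percentages above rest on assumed start times and lags.

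The practical route is narrow as well. A late joiner would have to learn the arm, obtain the registration link from the research team, register, consent, receive baseline access and finish, all before the survey closes. The article does not show that this happened, or that the platform allows it. This limits the likely size but does not make the stated rule deliver what it claims.

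Finally, the analysis gives partial protection. The primary test is a contrast of change from baseline, and substantially imbalanced baseline variables enter exploratory models. The baseline survey includes proxies for motivation, such as the perceived importance of training. These help with differences in starting level. They do not reliably remove a larger response among educators who joined because they knew the arm.

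**Conclusion.** The point holds in a limited form. In schools with more than one educator, the lock worded in the Registration section can fall after the arm is known in the school, so it does not guarantee the protection claimed for it. This follows from the order of events alone and needs no assumption about behavior.

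The size of any resulting selection cannot be determined from the article. The 0.015 to 0.03 SD illustration rests on two assumed inputs, and even then it is well under one fifth of a standard error, so a material effect on the primary result is unlikely. It would be wrong to conclude that selection bias occurred or that the trial's result is unsafe. What is wrong is the unqualified claim of prevention, together with two differently worded triggers. Both can be settled from time stamps.

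**What to change.** A new closing rule cannot help this trial, because baseline for waves 1 to 3 is complete and wave 4 is cancelled. The useful steps are retrospective.

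1. For each educator, compare the registration time with the first allocation email (or first baseline completion) in the same school. Report by arm how many registered after it.
2. Repeat the primary analysis excluding those educators in both arms. This removes late joiners but cannot recover colleagues who were put off by learning of the waitlist, so the counts by arm should be reported beside it.
3. In the Registration section and in Limitations and Strengths, state the single trigger that was actually applied, and limit the claim of prevention to what that trigger delivers.
4. For any future wave, close registration for a school no later than its first baseline start. Closure then precedes any completion, and the open period after disclosure is zero.

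The cost is one time-stamp check, one sensitivity analysis and two edited sentences. No sample-size figure changes. If nobody registered late, the check itself supports the article's claim.
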